### Compliance {11c}

We will issue CRFs to all subjects and supervise patients to fill CRFs every day to test compliance. Compliance with medication% = [actual dose/(specified daily dose × days)] × 100%. We will record the patient’s symptoms every day, and finally score according to CRFs. Messages will be sent through WeChat or by phone to remind the patients of the follow-up. Results of physical examinations will be explained at each visit. All the tests and drug fees during the trial will be covered.

### Combined use of drugs {11d}

During the study period, drugs with the same efficacy as the study drugs or related to the treatment of NERD will be prohibited to reduce intervention. If the subjects take drugs to control chronic diseases, such as hypertension and diabetes, they should truthfully and detailedly record the medication in the trial, including drug name (or other treatment name), dosage, frequency, and time of use.

### Outcomes {12}

#### Primary outcome measurements

##### GERD-Q scale score

GERD-Q scale is the most recognized and widely used special scale for GERD diagnosis in the world. In addition to diagnosing GERD, it can also evaluate the impact of GERD on quality of life and monitor the effect of treatment with high accuracy. A trained evaluator will record the evaluation at baseline, week 4, and week 8, fill out the GERD-Q questionnaire, and calculate the total score, frequency score, and degree score of GERD-Q symptoms. In the study, the score of GERD-Q scale after 8 weeks treatment will be used as the main outcome index.

#### Secondary outcome measurements

Quality of life score: According to the Chinese version of SF-36 health survey [19], the quality of life will be evaluated from 9 dimensions: physical function, physical function, physical pain, general health, vitality, social function, emotional function, and mental health. All the indexes will be recorded at baseline, week 4, and week 8.Patient-reported outcomes (PRO) self-rating scale score: There will be a diary card for patients to fill in every day. The researchers will calculate the PRO self-rating scale score according to the patient’s diary card at baseline, week 4, and week 8.TCM clinical syndrome score: According to the diagnostic criteria of cold-heat complex syndrome, the main and minor symptoms, tongue, and pulse will be graded and scored by using a unified table. All the indexes will be recorded at baseline, week 4, and week 8. According to the referred Guidance Principle of Clinical Study on New Drug of Traditional Chinese Medicine [20], all symptoms will be divided into four grades: none, mild, moderate, and severe, with 0, 2, 4, and 6 points in the main symptoms, and 0, 1, 2, and 3 points in the minor symptoms. In addition, the tongue and pulse will be divided into normal and abnormal grades, with 0 and 2 points.

The clinical efficacy will be evaluated as follows:
Clinical recovery: the symptoms disappeared or syndrome score decreased by ≥ 95% from the baseline.Marked efficacy: the syndrome score decreased by ≥ 70%, but < 95% from the baseline.Effective: the syndrome score decreased by ≥ 30%, but < 70% from the baseline.Ineffective: the symptoms and signs were not significantly improved, or even aggravated, and the syndrome score decreased by < 30% from the baseline.Aggravation: the syndrome score after treatment is higher than that before treatment.

TCM syndrome efficacy rate = (clinical recovery + marked efficacy + efficacy) cases/a total number of cases × 100%.
(4)Mechanistic outcome: The samples will be used to study the composition structure and metabolite expression profile of intestinal flora in NERD patients through 16s rRNA sequencing and metabonomic association analysis in TCM group, western medicine group at baseline and week 8, and in normal subjects at baseline. By analyzing the correlation between a variety of differential flora and differential metabolites, we will demonstrate the effects of changes in the structure of intestinal flora on metabolic phenotypes and functional metabolic small molecules. This experiment attempts to screen some key strains through visual tools, further explore their mechanism in the pathogenesis of NERD, identify the advantages of treatment, and reveal the potential mechanism of HWJNR. The determination of intestinal flora and metabolites will be performed by Shanghai OE Biotech Co., Ltd (Shanghai, China).(5)Follow-up recurrence index: The number and percentage of the subjects with non-medication, maintenance medication, intermittent medication, and on-demand medication will be recorded at month 1 and month 3 respectively.

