**Methods:**

This is a single-center, randomized controlled, double-blind, placebo-controlled clinical trial in which 72 eligible participants with NERD and TCM syndrome of intermingled heat and cold will be randomly allocated in the ratio of 1:1 to two groups: TCM group and western medicine group. The TCM group will receive HWJNR with omeprazole enteric-coated tablets placebo, while the western medicine group will receive omeprazole enteric-coated tablets with HWJNR placebo. Each group will be treated for 8 weeks. The primary outcome is the score of gastroesophageal reflux disease (GERD) health-related quality of life questionnaire (GERD-Q). Secondary outcomes include SF-36 quality of life scale (SF-36), patient-reported outcomes (PRO) self-rating scale score, syndrome score of TCM, and adverse events. Mechanistic outcome is the correlation analysis of intestinal flora and metabolites from healthy individuals and NERD participants before and after the treatment respectively.

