### Sample size {14}

According to clinical experience, the effective rate of NERD in the TCM group was P1 = 92.0%. The NERD effective rate of the western medicine group was P2 = 61.2% [(two-sided type I error rate of 0.05, *α* = 0.05); (one-sided type I error rate of 0.20, *β* = 0.20)]. The sample size is calculated by the following formula:
$$ n=\frac{2\overline{p}\overline{q}{\left({Z}_{\alpha }+{Z}_{\beta}\right)}^2}{{\left(P1-P2\right)}^2} $$

*n*1 = *n*2 = 2 × 0.766 × 0.234 × 2.8^2^ ÷ 0.308^2^ = 30. Taking approximate dropouts of 20% into account, the number of participants recruited was estimated to be 36 per group. Therefore, a total of 72 patients will be recruited in this trial. And we will additionally recruit 10 healthy controls.

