### Biological specimens {26b,33}

We will collect human samples including blood, urine, and feces. These samples will be used for blood routine test, urine routine test, stool routine test, and liver and kidney function test. The feces will additionally be used to detect the relationship between fecal flora and metabolites. All specimens will be destroyed after examinations.

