### Statistical analysis {20}

Efficacy analysis will be performed based on both FAS and PPS patients. Safety analysis includes all randomized participants who take at least one bag of HWJNR and have data for safety assessment. Comparing the healthy control group with the traditional Chinese medicine group, we will study the composition of the intestinal flora and the expression of metabolites in patients with NERD and the healthy group. And it will also reveal the mechanism of action and advantages of HWJNR in the treatment of NERD patients.

Changes from baseline to post-treatment in GERD-Q, SF-36, PRO, and syndrome score of TCM will be analyzed using analysis of covariance with associated 95% confidence intervals. All the analysis results will be generated by SPSS 25.0 software. Repeated measurement data are expressed by mean ± standard deviation, intra-group comparison is performed by analysis of variance of repeated measurement data, and inter-group comparison is by multivariate analysis of variance (MANOVA). *P* ≤ 0.05 indicates that the difference is statistically significant. Unilateral test will be used in all statistical tests, and the significance level *P* ≤ 0.05. The arithmetic mean, standard deviation, median, minimum, and maximum will be calculated according to the data distribution. Counting data will be used to calculate the number and percentage of cases.

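### Correlating flora and metabolites already picked as 'differential' cannot demonstrate that flora changes affect metabolites, and it inflates false findings if groups or time points are pooled

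*Protocol article*

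**What the plan says.** Item 4 of Secondary outcome measurements in the protocol article sets out the mechanistic outcome. Stool is assayed for flora and metabolites "in TCM group, western medicine group at baseline and week 8, and in normal subjects at baseline". The stated rule is: "By analyzing the correlation between a variety of differential flora and differential metabolites, we will demonstrate the effects of changes in the structure". The sentence goes on to name its target, the "effects of changes in the structure of intestinal flora on metabolic phenotypes and functional metabolic small molecules".

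Other places that bear on it:

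- Biological specimens: one specimen serves the flora-metabolite question. "The feces will additionally be used to detect the relationship between fecal flora and metabolites".
- Statistical analysis: one contrast is named, the same for both data types. "Comparing the healthy control group with the traditional Chinese medicine group, we will study the composition of the intestinal flora and the expression of metabolites".
- Abstract, Methods: "Mechanistic outcome is the correlation analysis of intestinal flora and metabolites from healthy individuals and NERD participants before and after the treatment respectively".

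The article does not say which contrast makes a feature 'differential', or whether the correlation is run within or across groups and time points.

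**The concern.** The rule has three parts: keep features that differ, correlate them, and conclude that one affects the other. The third does not follow from the first two, however the correlation is run. A taxon and a metabolite can both shift because treatment acts on each, because disease state goes with each, or because the metabolite acts on the taxon. All three can give the pattern that the plan would read as an effect of flora on metabolites.

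The selection step adds a second risk. Two features that both differ between the same groups are correlated across those groups when the data are pooled, even if they are unrelated among the patients of any one group.

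Clarifying the mechanism of HWJNR is a stated purpose of the trial. Pairs that share nothing but a group difference could be reported as that mechanism.

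**Working it through.** The plan gives no figure for this analysis, so there is none to reproduce.

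**Inputs**

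- 36 per randomised group, from Sample size: "the number of participants recruited was estimated to be 36 per group". The same section gives 30 per group before the dropout allowance.
- 10 healthy controls, from Sample size.
- Shift *d* between groups, in SD units: not in the documents. Assumed range 0.5 to 1.0, with 0 as a reference.
- Within each group, taxon and metabolite are assumed independent and normal, so every significant correlation is false.

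**Step 1: correlation induced by pooling.** Let a share *p* of the pooled sample come from one group, and let both features differ by *d* SD between the groups. The pooled covariance is p(1−p)d² and each pooled variance is 1 + p(1−p)d². Hence, in absolute size,

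r = p(1−p)d² / [1 + p(1−p)d²].

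- 36 v 36: p(1−p) = 0.25. At d = 1.0, r = 0.25/1.25 = 0.20. At d = 0.8, r = 0.16/1.16 = 0.14. At d = 0.5, r = 0.0625/1.0625 = 0.06.
- 10 v 36: p(1−p) = (10/46)(36/46) = 0.170. At d = 1.0, r = 0.170/1.170 = 0.15. At d = 0.8, r = 0.109/1.109 = 0.10. At d = 0.5, r = 0.0425/1.0425 = 0.04.

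**Step 2: selection plus pooling, by simulation.** Keep a taxon and a metabolite only if each differs between the groups at two-sided P < 0.05 (t-test). Then test their Pearson correlation at 0.05, first pooled and then with group means removed.

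| Groups | d = 0.5 | d = 0.8 | d = 1.0 | Group means removed |
|---|---|---|---|---|
| 36 v 36 | 12–13% | 24% | 41–42% | about 5% |
| 30 v 30 | 13% | 23% | 36% | about 5% |
| 10 v 36 | 13% | 17% | 22% | about 5% |
| 10 v 30 | 14% | 18% | 23% | about 5% |

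Entries are the share of kept pairs that are falsely significant; ranges cover repeat runs. The 30 per group rows show that dropout does not alter the picture. With no true shift (d = 0), selection alone gives 8% for 36 v 36 and 10% for 10 v 36.

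**Step 3: pooling time points.** The same test was run on baseline and week-8 samples from one arm (36 patients, assumed within-patient correlation 0.5). Pooling the two times gave 11.0%, 23.6% and 41.7% at d = 0.5, 0.8 and 1.0. Correlating each patient's change instead gave 4.9% to 5.0%.

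**The case against.** The strongest reply is that the plan never says that it pools. A reader might infer that the correlation is spurious by construction. The documents do not support that: pooling is neither stated nor excluded, and the word 'respectively' in the abstract may mean a separate analysis for each group and time. Purely within-group correlations would carry none of the induced part. This stands, so the percentages above are conditional.

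A reader might also infer that the plan leaves out correlation of changes, or wrongly omits a link to GERD-Q. The article is silent on both, and a condensed article may leave them to a fuller document. Silence is not the finding here. Nor is the hope that "This experiment attempts to screen some key strains through visual tools": the documents say nothing on the resolution of the assay.

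The shifts are assumptions, and the largest figures belong to 36 v 36. The contrast named in Statistical analysis is healthy controls against the TCM group, where the figures are lower.

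Finally, the surrounding text is hedged; it speaks of attempting, exploring and a potential mechanism. That softens the tone, but the sentence on demonstrating effects remains a stated inference. More analysis detail elsewhere could not make a correlation of preselected features support it.

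**Conclusion.** The stated conclusion does not follow from the stated analysis, and this holds whether or not data are pooled. The inflation in false findings holds only under pooling. With no within-group association, it is about 12% to 42% of kept pairs for 36 v 36 at assumed shifts of 0.5 to 1.0 SD, and about 17% to 22% for 10 v 36 at 0.8 to 1.0 SD, against about 5% with group means removed.

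The point concerns a mechanistic item among the secondary outcomes. The GERD-Q comparison, the sample size and the safety analysis are not touched. It is worth correcting because the mechanism is a declared aim and the stool samples that a better analysis needs are already planned.

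**What to change.** 1. Define the mechanistic analysis as the correlation, across randomised patients, of within-patient change (week 8 minus baseline) in a taxon with change in a metabolite, adjusted for arm (a partial correlation within arm).
2. Keep the 10 healthy controls for a baseline contrast outside this correlation. They give stool at baseline only and have no change to contribute.
3. State the conclusion as describing associations, in place of demonstrating effects. Step 1 removes the induced correlation, but it still gives neither direction nor causation, so the wording has to change as well.

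Relating these changes to change in GERD-Q is an optional exploratory addition; GERD-Q is recorded at both times.

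Cost: analysis and wording only, with no new samples or visits. Fewer pairs will be reported, patients without a week-8 stool sample drop out of the correlation, and the mechanistic claim is weaker.

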## Methods/design

### Study design and setting {8-9}

This is a single-center, double-blinded, placebo-controlled, randomized controlled trial (RCT), which will be conducted in Dongfang Hospital, Beijing University of Chinese Medicine. The study is conducted in accordance with the Declaration of Helsinki (Edinburgh 2000 version). The final protocol (Version 2.0, 11 November 2020) of this trial has been approved by Ethical Committee of Dongfang Hospital, Beijing University of Chinese Medicine (Version number: JDF-IRB-2020033602). In addition, this trial has been registered in the Chinese Clinical Trial Registry (No. ChiCTR2000041225, registered on 22 December 2020).

We aim to enroll 72 patients with NERD over a 2-year period (Date from November 2020 to December 2022) from the department of gastroenterology in Dongfang Hospital, Beijing University of Chinese Medicine. Eligible patients will be randomized at a ratio of 1:1 to either TCM group (HWJNR with omeprazole enteric-coated tablets placebo) or western medicine group (omeprazole enteric-coated tablets with HWJNR placebo) for 8 weeks treatment. At the end of this trial, the primary outcome (GERD-Q) and the secondary outcome (SF-36, PRO, syndrome score of TCM) will be evaluated. We will obtain peripheral venous blood, urine, and stool from NERD patients before and after treatment. This study involves 3 site visits (week 0, week 4, and week 8) and 10 call visits (weekly call during the treatment period and follow-up at month 1 and month 3). The process of the study is schematically shown in Fig. 1. And we will additionally recruit 10 healthy controls.

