### Interventions {11}

#### Intervention description {11a}

TCM group was given HWJNR with omeprazole enteric-coated tablets placebo; western medicine group was given omeprazole enteric-coated tablets with HWJNR placebo. The course of treatment is set for 8 weeks. Medication method and dose were as follows: omeprazole enteric-coated tablets/placebo: 20 mg, once a day, half an hour before breakfast; HWJNR/placebo: twice a day, one bag at a time, half an hour after breakfast and dinner. For production of formula placebo: the TCM placebo is made by Beijing Kangrentang Pharmaceutical Co., Ltd., according to the preparation process of HWJNR. The shape, color, gas, and taste will be similar to HWJNR after adding the same kind and equal amount of excipients. Finally, 5% of the original unit treatment drug is added to correct color and taste.

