## Discussion

The study is a single-center, randomized controlled, double-blind, placebo-controlled clinical trial for HWJNR to evaluate the efficacy and safety in the treatment of NERD. NERD is characterized by the presence of typical GERD symptoms associated with pathological acid reflux, including heartburn and regurgitation, but the absence of esophageal erosion [21, 22]. NERD presents in approximately 70% of patients with GERD, which has a great impact on life quality [3]. The high incidence of NERD and the widespread use of PPIs in clinical practice mean that the problems of complications and recurrence after drug withdrawal are increasingly common. TCM has a significant role in alleviating symptoms and maximizing quality of life of NERD patients. Hence, GERD-Q, SF-36, PRO, and syndrome score of TCM will be selected as therapeutic indicators, since they are correlated to the patients’ symptoms and quality of life.

HWJNR is mainly made up of Huangqin, Huanglian, Qingbanxia, Ganjiang, and other ten herbs. In our previous research, HPLC analysis was used to measure the contents of HWJNR. The results showed that the repeatability and stability of these main ingredients of HWJNR are good, and the quality is controllable [18]. Previous clinical studies have shown that HWJNR is safe and effective in NERD.

The factors that affect NERD have not yet been clarified [23]. There are several hypotheses about the etiology of NERD, such as esophageal visceral hypersensitivity, sustained esophageal contractions, and abnormal tissue resistance [24]. Recently, studies focus on abnormal microbial-brain-gut interaction and low-level inflammation of GERD mediated by hypoxia-inducible factor [25, 26]. We also expect to have a deeper understanding of the dominant links of treatment, reveal the potential mechanism of HWJNR, and study the composition structure and metabolite expression profile of intestinal flora in patients with NERD.

We aim to provide new and high-quality evidence in HWJNR for patients with NERD (cold-heat complex syndrome) through the clinical trial. The research results are expected to help formulate relevant clinical programs and corresponding guidelines. However, this study is a small sample size clinical study conducted in Beijing of China. Therefore, it is necessary to conduct multicenter clinical trials in further research.

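### End-of-treatment stool can carry HWJNR's own compounds, so correlating differential metabolites with differential flora cannot show that flora changes caused metabolic changes

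*Protocol article*

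**What the plan says.** All references are to the protocol article.

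- **Dosing (Intervention description {11a}).** "The course of treatment is set for 8 weeks", and "HWJNR/placebo: twice a day, one bag at a time, half an hour after breakfast and dinner". Table 1 lists ten herbs.
- **Control arm (same section).** The HWJNR placebo is not free of the drug: "Finally, 5% of the original unit treatment drug is added to correct color and taste".
- **Specimen (Biological specimens {26b,33}).** One specimen serves both measurements: "The feces will additionally be used to detect the relationship between fecal flora and metabolites".
- **Timing.** The mechanistic outcome is measured "in TCM group, western medicine group at baseline and week 8, and in normal subjects at baseline" (Secondary outcome measurements, item 4). Study design and setting {8-9} puts it this way: "We will obtain peripheral venous blood, urine, and stool from NERD patients before and after treatment". No interval since the last dose, washout or later stool sample is stated.
- **Inference (item 4).** "By analyzing the correlation between a variety of differential flora and differential metabolites, we will demonstrate the effects of changes" in the structure of the flora on metabolic phenotypes and functional small molecules. The same paragraph expects this to reveal how HWJNR works.
- **Constituents (Discussion).** "In our previous research, HPLC analysis was used to measure the contents of HWJNR".

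**The concern.** The metabolite list is selected for being different between groups or visits. In the TCM group, compounds that come from the ten herbs would differ from baseline simply because the patient has been taking the product. They would differ from the control arm because that arm receives about one twentieth of the herbal amount. A filter for differential features therefore favours them.

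The flora list is selected in the same way. When the two lists are correlated across arms or visits, treatment is a common cause of both. A herbal compound and a taxon can then correlate although neither acts on the other, and the stated reading would credit the compound to the flora.

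The article names clarifying the mechanism of HWJNR as a purpose of the trial. The risk is that markers of having taken HWJNR are reported as its mechanism.

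**Working it through.** The plan states no figure on this point, so there is none to reproduce. Two questions can be checked: how readily a herbal constituent would be called differential, and whether that alone creates a false link with flora.

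**Inputs from the article.** 5% of the drug in the HWJNR placebo; 36 patients per group; 20% dropout, which leaves 36 × 0.8 = 28.8, about 29 per group.

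**Assumptions, not in the article.** Fecal level proportional to intake; between-patient SD of 1.0 to 2.0 on the natural log scale; 1,000 metabolite features with Bonferroni correction; taxon shifts of 0.5 to 1.0 SD between arms.

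**Step 1: contrast between arms.** Intake ratio = 1/0.05 = 20, and ln(20) = 3.00. The standardised difference is d = 3.00/SD, which is 3.0, 2.0 and 1.5 for SDs of 1.0, 1.5 and 2.0.

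**Step 2: chance of being called differential.** Two-sample t test, two-sided alpha = 0.05/1000, non-centrality = d × √(n/2).

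| n per arm | SD 1.0 | SD 1.5 | SD 2.0 |
|---|---|---|---|
| 36 | 1.000 | 1.000 | 0.973 |
| 29 | 1.000 | 0.999 | 0.890 |

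Under these assumptions a herbal constituent almost always enters the metabolite list. This is not yet a false link with flora.

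**Step 3: chance of a false flora-metabolite link.** Let the metabolite differ by dm SD and the taxon by df SD between two equal arms, with no relation within either arm. The correlation in the pooled data is

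r = (dm × df/4) / √[(1 + dm²/4)(1 + df²/4)].

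Example: dm = 1.5 and df = 0.8 give 0.30/√(1.5625 × 1.16) = 0.22.

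Share of simulated data sets with a significant result (4,000 per row, 36 per arm, two-sided 0.05; Spearman test for pooled and within-arm, partial correlation for arm-adjusted):

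| dm | df | r | pooled | within one arm | adjusted for arm |
|---|---|---|---|---|---|
| 1.5 | 0 | 0.00 | 5% | 5% | 4% |
| 1.5 | 0.5 | 0.15 | 24% | 5% | 5% |
| 1.5 | 0.8 | 0.22 | 50% | 5% | 5% |
| 1.5 | 1.0 | 0.27 | 67% | 5% | 5% |
| 3.0 | 0 | 0.00 | 5% | 5% | 5% |
| 3.0 | 0.5 | 0.20 | 40% | 5% | 4% |
| 3.0 | 0.8 | 0.31 | 77% | 5% | 5% |
| 3.0 | 1.0 | 0.37 | 93% | 5% | 5% |

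**Step 4: effect of selecting the flora.** The article correlates only differential flora. A taxon with no true shift that passes a between-arm test at p < 0.05 by chance then correlates significantly with the herbal compound, in pooled data, in about 25% (dm = 1.5) to 46% (dm = 3.0) of data sets. The selection rule thus supplies much of the flora shift that a false link needs.

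**The case against.** **Filtering is pipeline detail.** An article need not describe feature annotation or removal of drug-derived compounds; the full protocol, the laboratory plan or the SAP may hold it. That is fair, and the missing filter alone would be no finding. What remains is what the article does state: it selects differential features, correlates them, and announces a directional effect of flora. That conclusion does not follow from that method.

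**Stronger readings go beyond the text.** A reader might infer that patients are still taking HWJNR when the week-8 stool is collected. The article describes sampling after treatment and gives no interval, so only end of treatment with no stated washout is supported. A reader might also infer that every herbal constituent will be found and will be misread as a flora effect. The article gives no fecal data on HWJNR: nothing on recovery, detectability or variability. Some compounds may be absorbed or degraded, and dietary sources of related compounds could shrink the 20-fold contrast.

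**The near-certain figures answer a different question.** The 0.97 to 1.00 in Step 2 is the chance of being called differential, not of a false mechanism. A false link also needs pooling across arms or visits and a flora difference in the data. The article does not say that data are pooled. It does not exclude pooling either, and features defined by group or visit differences invite it.

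**Deleting all drug-derived features could do harm.** Bacterial conversion of herbal compounds is plausibly part of what the mechanistic aim seeks. This stands, and the fix allows for it.

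**Conclusion.** The point holds in conditional form. HWJNR-derived compounds can be expected in the TCM group's week-8 stool and among the differential metabolites. If they are correlated with differential flora across arms or visits, flora-metabolite links can appear with no effect of flora. The claim that the correlation will demonstrate such an effect is not supported by this design.

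The size depends on assumptions. With metabolite shifts of 1.5 to 3.0 SD and taxon shifts of 0.5 to 1.0 SD, 24% to 93% of unrelated pairs would look linked in pooled data, against about 5% within one arm or after adjustment for arm. None of these shifts can be checked from the article.

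The scope is limited to one mechanistic outcome listed among the secondary outcomes. GERD-Q, the other clinical outcomes and safety are untouched. So is the comparison of patients with healthy subjects at baseline, before any study drug. The change is worth making because mechanism is a stated purpose and the remedy is cheap.

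**What to change.** In item (4), Mechanistic outcome:

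1. Before the flora correlation, flag metabolite features that match constituents of HWJNR, its placebo or omeprazole. Use the known constituent list, or reference runs of the product and placebo in the same metabolomics batch. The Discussion mentions only main ingredients from the HPLC work, so reference runs may be the more complete source.
2. Report the flagged features separately as exposure markers.
3. Run the main correlation on the remaining metabolites, within arm or adjusted for arm, and also for visit where visits are combined. Give the unfiltered result as a sensitivity analysis.
4. Label biotransformation products of herbal compounds and report them as their own class; do not delete them.
5. Replace the claim of a demonstrated effect with wording such as: we will describe associations between flora and metabolites; these do not establish that changes in flora cause changes in metabolites.

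If the full protocol or SAP already contains steps 1 to 4, only the wording in step 5 needs to change.

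The cost is a few reference runs and one extra analysis step, with no change for patients. Some compounds shared by the herbs, diet and host will be set aside from the main list; the sensitivity analysis shows what difference that makes.
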